## Abstract

**Background:**

Malnutrition and intestinal parasitic infections are common among children in Burkina Faso and Nepal. However, specific health-related data in school-aged children in these two countries are scarce. In the frame of a larger multi-stakeholder project entitled “Vegetables go to School: Improving Nutrition through Agricultural Diversification” (VgtS), a study has been designed with the objectives to: (i) describe schoolchildren’s health status in Burkina Faso and Nepal; and to (ii) provide an evidence-base for programme decisions on the relevance of complementary school garden, nutrition, water, sanitation and hygiene (WASH) interventions.

**Methods/Design:**

The studies will be conducted in the Centre Ouest and the Plateau Central regions of Burkina Faso and the Dolakha and Ramechhap districts of Nepal. Data will be collected and combined at the level of schools, children and their households. A range of indicators will be used to examine nutritional status, intestinal parasitic infections and WASH conditions in 24 schools among 1144 children aged 8–14 years at baseline and a 1-year follow-up. The studies are designed as cluster randomised trials and the schools will be assigned to two core study arms: (i) the ‘complementary school garden, nutrition and WASH intervention’ arm; and the (ii) ‘control’ arm with no interventions. Children will be subjected to parasitological examinations using stool and urine samples and to quality-controlled anthropometric and haemoglobin measurements. Drinking water will be assessed for contamination with coliform bacteria and faecal streptococci. A questionnaire survey on nutritional and health knowledge, attitudes and practices (KAP) will be administered to children and their caregivers, also assessing socioeconomic, food-security and WASH conditions at household level. Focus group and key-informant interviews on children’s nutrition and hygiene perceptions and behaviours will be conducted with their caregivers and school personnel.

**Discussion:**

The studies will contribute to fill a data gap on school-aged children in Burkina Faso and Nepal. The data collected will also serve to inform the design of school-based interventions and will contribute to deepen the understanding of potential effects of these interventions to improve schoolchildren’s health in resource-constrained settings. Key findings will be used to provide guidance for the implementation of health policies at the school level in Burkina Faso and Nepal.

**Trial registration:**

ISRCTN30840 (date assigned: 17 July 2015)

## Background

Malnutrition, intestinal parasitic infections and diarrhoeal diseases are common public health problems in children in low- and middle-income countries (LMIC) [1–8]. In many countries, Demographic and Health Surveys (DHS) and national nutrition surveillance systems have been measuring height and weight of children below the age of 5 years, starting in the early 1990s. However, there is a paucity of anthropometric data for school-aged children (5–14 years) [9–11]. Additionally, there are currently no estimates neither for school-aged children, nor the entire population, on the global burden of diseases from polyparasitism of intestinal parasitic infections caused by helminths and intestinal protozoa [7]. Data on the burden of disease caused by intestinal protozoa is scarce, partially explained by the lack of diagnosis at the periphery [12–15]. Although no estimates on the burden of diseases caused by helminth infections for school-aged children exist, an estimate for the burden of disease of sub-groups of helminth infections is available (e.g. schistosomiasis and soil-transmitted helminthiasis) [4, 7, 16]. Estimates from the Global Atlas of Helminth Infection (GAHI; http://www.thiswormyworld.org/) showed that, in 2010, 1.01 billion school-aged children lived in areas where prevalence of any soil-transmitted helminth (STH) was above 20 % [7]. Furthermore, in 2013, diarrhoeal diseases were responsible for an estimated 7 % of deaths in school-aged children in LMICs, with more than 96 % attributable to unsafe water, inadequate sanitation and hygiene (WASH) [4, 5].

Burkina Faso and Nepal are both low-income countries that face an array of similar health challenges. Whilst health data among under 5-year-old children, such as nutritional indicators, anaemia or *Plasmodium* prevalence, are collected during national surveys, statistics on school-aged children in these two countries are typically unavailable [17, 18]. Malnutrition, anaemia and diarrhoeal diseases are highly prevalent in under 5-year-old children. Indeed, according to the 2010 and 2011 DHS in Burkina Faso and Nepal, respectively, 35 % and 41 % of children were stunted; almost 15 % of children in both countries reported diarrhoea 2 weeks prior to a DHS; and 88 % of the children in Burkina Faso and 46 % in Nepal were anaemic [17, 18]. Both countries also face considerable ill-health due to inadequate WASH conditions. For example, according to data from the 2013 Global Burden of Disease Study (GBD) and the World Health Organization (WHO)/United Nations Children's Fund (UNICEF) ‘Joint Monitoring Programme for Water Supply and Sanitation’, 7 % and 8 % of deaths in children aged 8–14 years in Burkina Faso and Nepal, respectively, were caused by diarrhoeal diseases, with over 96 % in both countries attributed to inadequate WASH conditions as primary risk factor [4, 19]. Table 1 provides an overview of selected health and WASH indicators in Burkina Faso and Nepal for the years 2010 to 2013.

**Table 1 Tab1:** Overview of health and WASH indicators of Burkina Faso and Nepal: (a) Mortality rate among children aged 5 to 14 years old; (b) Disability-adjusted life year (DALYs) as indicator of morbidity among children aged 5 to 14 years old

Indicator	Burkina Faso	Nepal
Health	*DHS 2010*	*DHS 2011*
Stunting (<5 years)	35 %	41 %
Wasting (<5 years)	16 %	11 %
Underweight (<5 years)	26 %	29 %
Diarrhoea (<5 years)	15 %	14 %
Anaemia (<5 years)	88 %	46 %
Mortality (a) and morbidity [DALYs] (b)	*GBD 2013*	*GBD 2013*
Diarrhoeal diseases (5 to 14 years old)	7 % (a), 5 % (b)	8 % (a), 4 % (b)
Iron-deficiency anaemia (5 to 14 years old)	1 % (a), 6 % (b)	1 % (a), 15 % (b)
Intestinal infectious diseases (5 to 14 years old)	4 % (a), 2 % (b)	10 % (a), 4 % (b)
Water, sanitation and hygiene (WASH)	*DHS 2010 (a) and WHO Progress Report on Drinking-Water and Sanitation 2012 (b)*	*DHS 2011 (a) and WHO Progress Report on Drinking-Water and Sanitation 2012 (b)*
Improved latrines	15 % (a), 19 % (b)	38 % (a), 37 % (b)
Non-improved latrines	6 % (a), 17 % (b)	43 % (a), 6 % (b)
Open defaecation (bush/field, no latrines)	62 % (a), 57 % (b)	36 % (a), 40 % (b)
Soap and water for hand washing available	14 % (a)	48 % (a)

(a) Mortality rate among children aged 5 to 14 years old

(b) Disability-adjusted life year (DALYs) as indicator of morbidity among children aged 5 to 14 years old

Malnutrition, intestinal parasitic infections and inadequate WASH conditions are intricately linked. First, inadequate WASH conditions are important risk factors for both, malnutrition and intestinal parasitic infections [2, 4, 15, 20, 21]. The pathogenic agents associated with poor WASH conditions are viral pathogens, bacterial pathogens, protozoan cysts or oocysts and helminth eggs found in faeces and transmitted through the faecal-oral pathway and can lead to diarrhoea and undernutrition, whereby exposure to one increases vulnerability to the other [22–27]. Second, malnutrition can render a child more susceptible to infection. An inadequate dietary intake leads to weight loss, weakened immunity, invasion by pathogens and mucosal damage, and impaired growth and development in children [28–30]. Third, parasitic infections also contribute to growth stunting by causing a decline in food intake (loss of appetite), diarrhoea, malabsorption and/or an increase in nutrient wastage for the immune response, all of which lead to nutrient losses and further damage to the defence mechanisms, causing a vicious cycle [28–30]. Moreover, it is well documented that infections with intestinal parasites may cause internal bleeding, leading to a loss of iron and anaemia [31, 32]. Intestinal parasitic infections can go unnoticed for years due to delayed onset of symptoms, which can exacerbate the effects on malnutrition, and hence compromise the development of their cognitive abilities in their formative years [30]. It is therefore crucial to consider the strong interlinkages of malnutrition, parasitic infections, diarrhoeal diseases and WASH for preventive actions and sustainable programmes.

### “Vegetables go to School: Improving Nutrition through Agricultural Diversification”

A multi-country and multi-stakeholder project entitled “Vegetables go to School: Improving Nutrition through Agricultural Diversification” (VgtS in short) was developed and is funded by the Swiss Agency for Development and Cooperation (SDC) to address schoolchildren’s nutrition in an interdisciplinary approach through the implementation of school vegetable gardens and other school-based health, nutrition and environmental interventions. The VgtS project was launched in 2012 in six target countries (Bhutan, Burkina Faso, Indonesia, Nepal, the Philippines and Tanzania) and is implemented by country teams composed of members of different ministries, (i.e. education, agriculture and health), in collaboration with the World Vegetable Center (AVRDC; headquartered in Taïwan), the University of Freiburg in Germany and the Swiss Tropical and Public Health Institute (Swiss TPH) in Switzerland as academic partners.

The objectives of the VgtS project are threefold: (i) to encourage agricultural production at the unit of the school and to increase the availability and access to a wide diversity of vegetables in order to favour a balanced and nutritious diet; (ii) to link the school garden to an educational programme that covers basic topics of agriculture, nutrition and WASH (overall project approach in all the countries); and (iii) to link the school garden programme to complementary nutrition and WASH interventions. In this context, the VgtS project embeds two intervention studies in Burkina Faso and Nepal, which include intervention schools benefitting from a complementary school garden, nutrition and WASH intervention package and control schools without any intervention. Here, we present the research protocol for the studies in Burkina Faso and Nepal.

## Methods/Design

### Goal

The overarching goal of the studies within the frame of the VgtS project in Burkina Faso and Nepal is to address the current data gap on schoolchildren (aged 8–14 years) and to assess the effects of complementary school garden, nutrition and WASH interventions on schoolchildren’s health status, as assessed by a baseline and a 1-year follow-up survey through a range of previously identified nutrition, WASH and health indicators (Table 2).

**Table 2 Tab2:** Selected indicators for the two studies in Burkina Faso and Nepal

Objective	Indicator	Methods and tools	Survey module
*Individual level of child*			
To assess schoolchildren’s nutritional status at baseline and follow-up	Nutritional status (BMIZ, HAZ, WAZ and clinical signs of malnutrition)	Digital scale, height measuring board and clinical examination	Nutritional survey (module 1)
To assess the prevalence of anaemia in schoolchildren at baseline and follow-up	Anaemia based on haemoglobin levels < 11.5 g/dl for children aged 7 to 11 years and < 12 g/dl for those aged 12 to 14 years	HemoCue Hb 201^+^	Nutritional survey (module 1)
To assess the prevalence of intestinal parasitic infections in schoolchildren at baseline and follow-up	Presence and intensity of intestinal and urinary parasitic infections	Kato-Katz and formalin-ether concentration method for stool samples and centrifugation method for urine samples	Parasitological survey (module 2)
To assess schoolchildren’s nutrition and health knowledge, attitudes and practices (KAP) at baseline and follow-up	KAP related to nutrition and health	Questionnaire survey with schoolchildren Focus group discussions with schoolchildren In-depth interviews with school directors and teachers	Children’s health KAP (module 3)
*Environmental indicators*			
To assess drinking water quality of children’s drinking water recipients at baseline and follow-up	Presence of thermotolerant coliform bacteria and faecal streptococci	Portable DelAgua field kit and RAPID E. COLI 2 AGAR (coliform bacteria, *Escherichia coli*) and Bile Esculine Azide AGAR (faecal streptococci) tests	Water quality testing (module 4)
*Household level*			
* Demographic and socioeconomic data*			
To assess basic household socio-demographic and economic characteristics at baseline and follow-up	Caregiver’s age, educational level, occupational status, assets, food security	Household questionnaire	Household questionnaire survey (module 5)
* Household nutrition and health -related knowledge, attitudes and practices data*			
To assess caregivers’ nutrition and health knowledge, attitudes and practices at baseline and follow-up	Caregiver’s knowledge, attitudes and practices related to nutrition and health	Household questionnaire Focus group discussions with schoolchildren’s caregivers	Household questionnaire survey (module 5) Caregivers’ health knowledge, attitudes and practices (module 6)
* Socio-environmental conditions data*			
To assess household WASH conditions at baseline and follow-up	Drinking water source and distance to it, water storage, improved/non-improved latrine, location of kitchen, available hand washing facilities and soap, presence of domestic animals	Household living condition and information related to hygiene Direct observation	Household questionnaire survey (module 5)
* Environmental indicators*			
To assess drinking water quality at schoolchildren’s households at baseline and follow-up	Presence of thermotolerant coliform bacteria and faecal streptococci	Portable DelAgua field kit and RAPID E. COLI 2 AGAR (coliform bacteria, *Escherichia coli*) and Bile Esculine Azide AGAR (faecal streptococci) tests	Water quality testing (module 4)
*School and community level*			
* Socio-environmental conditions data*			
To assess the WASH conditions at schools at baseline and follow-up	Available drinking water, available improved/non-improved toilet/latrine, available hand washing facilities and soap	In-depth interviews with school directors and teachers Direct observation	WASH survey (module 7)
* Environmental indicators*			
To assess drinking water quality at schools and community sources at baseline and follow-up	Presence of thermotolerant coliform bacteria and faecal streptococci	Portable DelAgua field kit and RAPID E. COLI 2 AGAR (coliform bacteria, *Escherichia coli*) and Bile Esculine Azide AGAR (faecal streptococci) tests	Water quality testing (module 4)

### Study sites and school selection

The studies will be conducted in Burkina Faso and Nepal. The study sites are located within the VgtS project sites, which were selected by the local VgtS country teams, following a set of criteria: (i) accessibility from the capital; (ii) availability of land for the school garden and continuous access to water at schools; (iii) coeducation of boys and girls in public schools; and (iv) willingness of the school principals and the community to participate.

In both countries, the study will be implemented in two different regions. In Burkina Faso, these are the Centre Ouest and the Plateau Central regions, both located in proximity to the capital Ouagadougou (30–180 km). The study sites in Nepal are the Dolakha and Ramechhap districts in the eastern part of the country, both located in proximity of the district headquarters Charikot (133 km) and Manthali (131 km), respectively.

The selection of the schools participating in the two studies is based on a three-stage sampling procedure of schools within the overall VgtS project sites. In a first step, about 100 schools fulfilling the aforementioned eligibility criteria were selected. In a second step, from these 100 schools, a sample of 30 schools were randomly chosen to be included in the VgtS school garden implementation and were randomly allocated to three groups, which receive the school vegetable garden interventions in 2014, 2015 and 2016, respectively. In a third step, out of the 30 VgtS project schools, a total of eight schools in Burkina Faso and 16 schools in Nepal were randomly selected to accommodate the sampling needs of the two complementary and slightly different study designs of Burkina Faso and Nepal (Fig. 1).

**Fig. 1 Fig1:**
[figure not shown]
Study design for Burkina Faso and Nepal

### Study design

The two studies in Burkina Faso and Nepal are designed as cluster randomised trials with an equal number of schools randomly allocated to two core study arms (A, B) and with a cohort of children followed in two consecutive surveys, at baseline and 1-year follow-up. Two additional study arms are included in Nepal (C, D). The four study arms are designed as follows:arm A: school garden programme and complementary nutrition and WASH interventions;arm B: no interventions, i.e. controls;arm C: school garden programme without nutrition and WASH interventions; andarm D: nutrition and WASH interventions without the school garden programme.

Each arm comprises four schools. Figure 1 shows the study design with the different study arms for Burkina Faso and Nepal. In both countries, schools of arm A will receive the complementary school garden, nutrition and WASH intervention package starting in March 2015. In Nepal, the interventions from arms C and D will be implemented over the same period. In both countries, the control schools of arm B will benefit from the school garden intervention in the year following the interventions.

### Sample size

Two separate sample size calculations were conducted for the two study designs of Burkina Faso and Nepal. For the sample size calculation of the study in Burkina Faso, the prevalence of intestinal parasitic infection in children aged 8–14 years was selected as the primary outcome in the comparison between high- and low-risk of intestinal parasitic infection in children. The power calculation was based on the assumption of:an average intestinal protozoa and helminth infection rate across schools of 40 % [33];a coefficient of variation of 10 % across schools; anda proportion of high risk children of 25 %.

A Monte Carlo simulation with 5000 iterations shows that a total of 400 children from eight schools (i.e. 50 children per school) would provide 85 % power for detecting a significant difference in infection rates between high- and low-risk children at the usual level of 5 % under these assumptions and for a true odds ratio of 2. Recruitment will be increased by 10 % to account for drop-outs or non-participation, which leads to an optimal sample size of at least 440 children.

The sample size calculation for the study in Nepal was also based on the prevalence of intestinal parasitic infections in children aged 8–14 years as the primary outcome. The power calculation was based on the assumption of:the prevalence rate of intestinal protozoa and helminth infection is 30 % [34] and this rate will remain in steady state in the absence of any intervention;probability of new intestinal protozoa and helminth infection at the 1-year follow-up will be reduced by at least 10 % through the implementation of the complementary nutrition and WASH intervention package; anda coefficient of variation of 10 % across schools.

A Monte Carlo simulation with 5000 iterations shows that a total of 640 schoolchildren from 16 schools (i.e. 40 children per school) would provide 80 % of power for detecting a significant difference in infection rates between the four study arms. Recruitment will be increased by 10 % accounting for drop-outs and non-participants, which leads to an optimal sample size of at least 704 children.

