### Data collection procedures

Four weeks prior to the study, district and village authorities, school directors and children’s parents/guardians will be informed about the forthcoming survey activities by the local survey team. They will be re-informed about the purpose and procedures of the study shortly before the start of the survey activities. Written informed consent (signed or fingerprint) will be obtained from children’s parents or legal guardians, whilst children will assent orally. It will be emphasised that participation is voluntary and that children and parents/guardians can withdraw anytime without further obligation.

In each school, a random selection of children aged 8–14 years will be enrolled until at least 55 in Burkina Faso and 44 in Nepal are reached. Moreover, at the follow-up survey, the same children will be re-assessed, who by then will be 9–15 years old. Each child will be attributed a unique identification code (ID) for the different assessments at the onset of the study. A separate household ID connected to the schoolchild’s personal ID will be given to children’s households in order to link children’s clinical data and nutritional and health knowledge, attitudes and practices (KAP) with the household characteristics. Children will thereafter be invited to provide stool and urine samples, to take anthropometric and haemoglobin (Hb) measurements and to participate in the KAP survey. In Burkina Faso, stool and urine samples will be collected on two consecutive days. In Nepal, a single stool sample will be collected, while urine samples will not be collected as urogenital schistosomiasis is not endemic. Infected, anaemic or undernourished children in all schools will be subjected to clinical, parasitological and nutritional examinations, and will be treated according to national policies.

After these assessments with children at the schools, the same enumerators in Burkina Faso will visit children’s households and will invite children’s caregivers to respond to a household questionnaire during the two survey days. In Nepal, due to the scattered locations and geographical constraints, additional enumerators will visit the children’s households during the same survey period. In both countries, trained and experienced enumerators will conduct the questionnaire surveys in local languages.

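### Nepal: the 80 % power assumes a 30 % infection rate held steady without any intervention, but infected children in every school, controls included, are to be treated

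*Protocol article*

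**What the plan says.** Three places in the Protocol article bear on this.

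- **Sample size (Nepal).** Baseline prevalence of protozoa and helminth infection is taken as 30 %, and the article assumes that "this rate will remain in steady state in the absence of any intervention". The effect is placed on incidence, by 10 % or more, and is credited to the nutrition and WASH package. Between-school variation enters as "a coefficient of variation of 10 % across schools". The result given is that "a total of 640 schoolchildren from 16 schools (i.e. 40 children per school) would provide 80 % of power"; the contrast it names is among all four arms.
- **Study design.** The comparator is "arm B: no interventions, i.e. controls". One cohort of children is surveyed at baseline and again at one year, with four schools per arm.
- **Data collection procedures.** On those found to be infected, anaemic or undernourished, the text reads: "children in all schools will be subjected to clinical, parasitological and nutritional examinations, and will be treated according to national policies". The follow-up survey re-assesses the same children.

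**The concern.** A steady state is a balance: new infections replace those that clear. Treating the infections found at baseline adds clearance that the balance does not contain. The children whose control rate is held at 30 % are the same children who are treated when found infected. The assumption carries its own condition, absence of any intervention, and the data-collection section removes that condition in arm B as in every other arm.

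Two things are at stake. The first is the stated power for the primary outcome, which depends on the control rate at one year and on how many follow-up infections are new rather than persistent. Treatment changes both. The second is interpretation: the trial estimates what the package adds to screening and treatment given everywhere, and a fall from baseline within an arm may come partly from that treatment.

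**Working it through.** **Inputs from the article (Nepal).** Prevalence 30 %; reduction of at least 10 % in new infection; CV 10 % across schools; 40 children in each of 16 schools; four schools and so 4 × 40 = 160 children per arm; power 80 %. A two-sided 5 % level is assumed, because the article gives 5 % only for Burkina Faso.

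**Step 1: the plan's own figure, at an undisturbed 30 %.** ICC = CV² × p/(1 − p) = 0.01 × 0.3/0.7 = 0.0043. Design effect = 1 + 39 × 0.0043 = 1.17. For the four-arm test (3 df), the noncentrality is n × Σ(pᵢ − p̄)² / [p̄(1 − p̄)].

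- 10 points lower in the two nutrition/WASH arms (A and D): 160 × 0.01/0.1875 = 8.53, power 0.69; with the design effect 7.31, power 0.61.
- 10 % relative reduction (30 % to 27 %) in the same arms: power 0.10, or 0.09 with the design effect.
- A and D pooled against B and C (8 v 8 schools, 320 v 320 children), 30 % v 20 %: 0.83 ignoring clustering, 0.77 with the design effect, 0.72 by simulation with a t-test on school proportions, 0.82 by simulation with a test that ignores schools.

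So 80 % is not reproduced for the four-arm comparison. It is approached only by the pooled contrast when the test ignores clustering. That is a separate matter. It is noted here because the starting level below is 0.72.

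**Step 2: how far treatment could move the control rate.** The article gives no cure, clearance or reinfection rates, so these are assumptions. Take a two-state model with clearance rate ρ = 1/D (D = mean infection duration in years) and acquisition rate ρ × 0.3/0.7, which keeps 30 % steady. Then k = acquisition + clearance = ρ/0.7, and a group that starts at p₀ after treatment has p(1) = 0.30 + (p₀ − 0.30)e^(−k).

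| D | k | p(1), all cured (p₀ = 0) | p(1), half cured (p₀ = 0.15) |
|---|---|---|---|
| 3 months | 5.71 | 29.9 % | 30.0 % |
| 6 months | 2.86 | 28.3 % | 29.1 % |
| 1 year | 1.43 | 22.8 % | 26.4 % |
| 2 years | 0.71 | 15.3 % | 22.7 % |

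The shift can be negligible or can halve the rate.

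**Step 3: what a lower control rate does to power.** Simulation with a t-test on school proportions, CV 10 %, 40 per school, 8 v 8 schools:

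| Control rate at 1 year | Constant one-third reduction | Constant 10-point reduction | Constant 10 % relative reduction |
|---|---|---|---|
| 30 % | 0.72 | 0.72 | 0.11 |
| 25 % | 0.63 | 0.81 | 0.09 |
| 20 % | 0.54 | 0.90 | 0.08 |
| 15 % | 0.41 | 0.98 | 0.08 |

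With 4 v 4 schools, control rates of 30, 20 and 15 % give 0.38, 0.26 and 0.20 under the one-third reduction, and 0.38, 0.54 and 0.70 under the 10-point reduction. The one-third figure is 30 % to 20 % read as a ratio; the article does not state it.

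**Step 4: taking the effect on new infection literally.** If nobody is treated, a 10-point cut in the probability of new infection acts only on the 70 % who start uninfected: 0.7 × 0.10 = 0.07, so 30 % falls to 23 %. In a once-a-year step model, power for 8 v 8 schools is then 0.41 to 0.43. If all are cured, the cut acts on everyone. With 40 % to 70 % of infections clearing in a year, the contrast is 17.1 % v 7.1 % up to 30 % v 20 %, and power is 0.95 down to 0.72. Treatment therefore changes the contrast as well as the control rate.

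**The case against.** The best defence has four parts.

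- **The arms are labelled by study package.** No intervention in arm B can fairly mean no garden, nutrition or WASH programme, with treatment as openly stated care in all schools. This stands. A reader might infer that arm B is mislabelled or the comparison biased; the article does not support that, since care given alike in every arm leaves the randomised comparison fair. It does not restore the 30 % steady state, however.
- **The effect is set on new infection.** The planners may have allowed for clearance in the simulation. This is possible, but the text neither says so nor mentions treatment.
- **The shift may be trivial.** Reinfection may be fast, or national policies, which the article does not set out, may cover few of the organisms counted. This stands as to size. The one-year control rate could remain close to 30 %.
- **Arms are compared at the end of the year.** The data-analysis section says so, and nothing in the article presents a before-after change within an arm as the intervention effect. This stands, so misreading such a change is a risk of interpretation and not an error in the plan.

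The tempting stronger reading is that treatment leaves the trial underpowered. That follows only under a constant relative reduction. Under a constant 10-point reduction, an equally open reading of the same sentence, power rises.

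**Conclusion.** The point holds for Nepal as an assumption that the protocol's own procedures do not meet. The 30 % steady state is conditional on no intervention, infected children in arm B are treated, and the 80 % power is stated without a control rate that takes this into account. This takes the treatment to follow the baseline findings, which is the natural reading of the data-collection section.

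Neither the size nor the direction of the consequence is established. The one-year control rate of roughly 15 % to 30 % rests on assumed full cure, a two-state model and infection durations of 2 years to 3 months. Moving the control rate from 30 % to 20 % gives 0.72 to 0.54 or 0.72 to 0.90 (8 v 8 schools), depending only on the effect scale, which the article leaves open.

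A reader might extend the point to Burkina Faso. That calculation compares high-risk with low-risk children and makes no steady-state assumption, so the point does not apply there. The correction is worthwhile and cheap, but the validity of the between-arm comparison does not depend on it.

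**What to change.** Reconcile the Study design, Sample size and Data collection sections for Nepal:

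1. Replace the steady-state assumption with the control rate expected at one year given the treatment described, and state the assumptions on cure and reinfection behind it.
2. Say whether the 10 % reduction in new infection is absolute or relative.
3. Rerun the simulation over control rates of about 10 % to 30 % and restate the power.
4. State that the effect is that of the package added to baseline screening and treatment in every arm, judged between arms at follow-up.

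The cost is one simulation rerun and a few sentences. The restated power may come out lower or higher than 80 %. No change to care is proposed.

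### Nepal sample size: the outcome is infection prevalence but the assumed effect is on new infection, and nothing stated links the two, so the 80 % power is not supported for the named outcome

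*Protocol article*

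**What the plan says.** The Sample size section of the protocol article says that the Nepal calculation "was also based on the prevalence of intestinal parasitic infections in children aged 8–14 years as the primary outcome". Table 2, under Goal, agrees; its objective is "To assess the prevalence of intestinal parasitic infections in schoolchildren at baseline and follow-up".

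The assumptions listed for Nepal are:

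- "the prevalence rate of intestinal protozoa and helminth infection is 30" per cent, and "this rate will remain in steady state in the absence of any intervention";
- the "probability of new intestinal protozoa and helminth infection at the 1-year follow-up will be reduced by at least 10" per cent, through the nutrition and WASH package;
- a "coefficient of variation of 10 % across schools".

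From these, a simulation of 640 children in 16 schools (40 per school) "would provide 80 % of power for detecting a significant difference in infection rates between the four study arms".

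Two other sections bear on the point. Study design gives four schools per arm and a cohort surveyed twice. Data collection procedures has the same children re-assessed at one year, with no restriction to those negative at baseline, and says that infected children in all schools are treated under national policies. No cure, persistence or reinfection rate appears anywhere.

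**The concern.** Prevalence at follow-up counts every infected child, whether the infection is old, recurrent or new. The probability of new infection concerns children who are at risk of acquiring one. With 30 % of the cohort positive at baseline (0.30 × 640 = 192 children), the two quantities move together one for one only under particular conditions, and the article states none.

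What is at stake is whether the 80 % power belongs to the outcome that the study names. If the effect on new infection reaches only the 70 % who start uninfected, the prevalence contrast is smaller than the assumed effect. A study sized on the undiluted figure would then be short of power. The unstated scale of the 10 % (relative or percentage points) widens the uncertainty further.

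**Working it through.** **Inputs.** From Sample size: control prevalence 30 %, steady; reduction 10 %; CV 10 % across schools; 640 children, 16 schools, 40 per school. From Study design: 4 schools per arm. Assumed here: two-sided 5 % (the level is stated only for Burkina Faso), and a contrast of the arms with the nutrition and WASH package (A, D) against those without it (B, C), 8 v 8 schools. The article does not name the contrast; this one is the most favourable.

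**The plan's own figures.** 640 × 1.1 = 704 reproduces. The 80 % cannot be fixed from the stated inputs. The nearest match is prevalence 30 % v 20 % with 320 v 320 children: 83 % ignoring clustering, and 77 % with the design effect. The ICC is (0.10 × 0.30)² / (0.30 × 0.70) = 0.0043, so the design effect is 1 + 39 × 0.0043 = 1.167.

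**From new infection to prevalence.** Let λ be the probability of infection at one year in baseline-negative children, and π the probability that a baseline-positive child is infected at one year (persistent or reinfected). Then

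follow-up prevalence = 0.70 λ + 0.30 π = 0.30 in control schools.

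Neither λ nor π is given.

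- *10 percentage points, benefit in baseline-negatives only:* fall = 0.70 × 10 = 7 points, to 23 %. This needs λ ≥ 0.10, so π ≤ 0.23/0.30 = 0.767.
- *10 percentage points, benefit in all children:* fall = 0.70 × 10 + 0.30 × 10 = 10 points, to 20 %. One route is complete clearance followed by a common risk, λ = π = 0.30, cut to 0.20.
- *Relative 10 %, baseline-negatives only:* fall = 0.70 × 0.10 λ = 0.07 λ. The largest λ is 0.30/0.70 = 0.429 (π = 0), so the fall is at most 3 points, to 27 %.
- *Relative 10 %, all children:* 0.10 × 30 = 3 points, again 27 %.

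**Power for prevalence, 8 v 8 schools.** The variance of a school proportion is p(1−p)/40 + (0.10p)². Power = Φ(difference/SE − 1.96), with SE² = (sum of the two variances)/8.

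| Prevalence | Sum of variances | SE | Difference/SE | Power, normal approximation | Power, simulated school-level t-test |
|---|---|---|---|---|---|
| 30 % v 20 % | 0.00615 + 0.00440 | 0.0363 | 2.75 | 79 % | 72 % |
| 30 % v 23 % | 0.00615 + 0.00496 | 0.0373 | 1.88 | 47 % | 42 % |
| 30 % v 27 % | 0.00615 + 0.00566 | 0.0384 | 0.78 | 12 % | 12 % |

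For 80 % power with clustering, 30 % v 20 % needs about 343 children per group and 30 % v 23 % about 727; 320 are available.

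**Less favourable contrasts.** For 30 % v 20 %, one arm against another (160 v 160) has 48 % power with the design effect and 37 % by simulated t-test. A four-arm test on 3 degrees of freedom, with two arms at 20 % and two at 30 %, has 61 %.

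**Adjustment for baseline infection.** In the 7-point case, adjustment helps more as π rises. Simulated power reaches about 67 % at most and stays below 80 %.

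**The case against.** The best defence has three parts.

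First, infected children in all schools are treated after the baseline survey. If treatment clears them and they then face the same risk as the others, infection at one year is all new. The two quantities coincide, and a 10-point cut lowers prevalence by 10 points. This is coherent, and it is why 7 points is not the only answer on the absolute scale. But the article gives no cure rate and does not say that treatment entered the calculation. Under this account prevalence holds at 30 % only if reinfection happens to be 30 % a year.

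Second, an effect assumption is not an endpoint. A simulation may use new infection as its driver and test prevalence, with any dilution already built in. That is legitimate, and it means that the 80 % can be neither confirmed nor refuted from the text. It does require values for λ and π, and the result depends heavily on them.

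Third, a journal article need not print every simulation input. That is fair for detail. Here, however, the assumptions that are printed do not describe an effect on the named outcome.

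Some stronger readings are tempting but not supported:

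- *The report could choose between two primary endpoints.* Prevalence is named as the primary outcome and new infection is never called an outcome, so this would be speculation.
- *The reference to infection rates in the power sentence is a third endpoint.* The Burkina Faso paragraph uses the same looser term for an outcome that it names as prevalence.
- *An analysis of new infection would lack power.* With a 10-point cut in baseline-negatives (224 v 224), power runs from 54 % to 92 % as π goes from 0 to 0.65, so no single figure can be given.

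**Conclusion.** The point holds as a mismatch between the named outcome and the stated effect, with no stated link between them. The 80 % is approached for prevalence (72–79 % with clustering, 83 % without) only if the 10 % means percentage points, the reduction applies to every child, and the arms are pooled 8 v 8. The article states none of these three conditions. If only baseline-negative children benefit, power is about 45 % unadjusted. If the 10 % is relative, it is about 12 % at best.

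A reader might infer from the near match at 30 % v 20 % that the new-infection effect was simply applied to prevalence. The match suggests this but does not prove it. Nor do the documents show that the study is underpowered; they show that the stated power is not supported for the named outcome. The figures rest on a two-sided 5 % level, the pooled contrast and a CV of 10 %. The 7-point figure also assumes no benefit in baseline-positive children.

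**What to change.** 1. Keep infection prevalence at one year, in all re-assessed children, as the single primary endpoint for Nepal, with baseline infection status (already collected) as a covariate.
2. Restate the effect as follow-up prevalence in control and in intervention schools, in percentage points. Give the clearance and reinfection assumption behind it, including how the treatment of infected children was handled, and name the contrast tested among the four arms.
3. Re-run the simulation for the existing 640 children and restate the power, showing a range for the persistence assumption.
4. If new infection is analysed, make it secondary and restrict it to children negative at baseline (about 0.70 × 640 = 448), with that denominator stated.

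The cost is some rewording and one re-run of the simulation, with no new data and no more children. The drawback is that the stated power will probably look less favourable.
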